### Interventions

Once randomised, men allocated to the Babystart® FertilMate™ Scrotum Cooling Patch group will be provided instructions on its use and asked to apply the scrotal cooling patch nocturnally for a period of 90 consecutive days. They will also be advised to implement any other general lifestyle changes suggested by the clinician following the clinic consultation.

### Comparisons

Men randomised to the control group will not be given the Babystart® FertilMate™ Scrotum Cooling Patches to wear for 90 days but will be advised to implement any other general lifestyle changes suggested by the clinician following the clinic consultation.

### Follow-up

All participants will be reviewed in the fertility clinic after 90 days of wearing or not wearing the scrotal cooling patches and the following variables will be recorded on the research proforma: medical history, cigarette and alcohol use in the preceding 90 days, and body mass index. A semen analysis will be performed according to the standard clinic protocols for the sperm count, motility and morphology. A blood sample will be collected for endocrine variables including testosterone, follicle stimulating hormone and luteinising hormone. Serum samples will also be collected for metabolomic biomarkers and a three-dimensional ultrasound scan of the scrotum will be performed to evaluate scrotal testicular blood flow, volume and morphology.

### Outcome measures

The primary outcome measure will be the change in sperm concentration after 90 days in men wearing the Babystart® FertilMate™ Scrotum Cooling Patch compared to men not wearing the scrotal cooling patch. Secondary outcome measures will include the change in sperm volume, motility and morphology. Other secondary outcome measures will include the change in endocrine parameters (testosterone, follicle stimulating hormone and luteinising hormone), metabolomics biomarkers, testicular volume and blood flow as measured on three-dimensional ultrasound. Statistical correlations between testicular volume, blood flow and metabolomics biomarkers and semen parameters will also be evaluated. The number of potentially eligible men seen at each clinic will be noted and the proportion of these who consented to the study and completed the study will also be evaluated. Reasons for dropping out and non-compliance will also be noted and reported.

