### Study design

The study was designed as a randomised controlled trial and no stratification will be used.

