### Participants

The proposed sample size is 40 men with mild, moderate or severe oligoasthenospermia, with 20 men in the experimental group using the scrotal cooling patch and 20 men in the control group and not receiving the scrotal cooling patch. The inclusion criteria include men presenting to the fertility clinic with mild, moderate or severe oligoasthenospermia (sperm motility of < 32% and count of <15 million per millilitre), aged 18 to 45 years of age. Exclusion criteria include men who have undergone a vasectomy or have had any surgery to their genitalia, have an allergy to menthol, are aged below 18 or older than 45 years of age, are unable to consent for themselves, from vulnerable groups or with a chronic medical condition, for example diabetes or hypertension.

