### Pre-randomisation data

Baseline clinical demographics will be collected from the participant’s medical records and through a clinical interview, including age, occupation, medical history, cigarette use, alcohol intake, body mass index and a working clinical diagnosis. The results of the baseline semen analysis justifying inclusion into the study will be recorded in the research proforma and a blood sample will be collected for endocrine variables, including testosterone, follicle stimulating hormone and luteinising hormone. Serum samples will also be stored at −80°C for metabolomic biomarkers and a three-dimensional ultrasound scan of the scrotum will be performed to evaluate scrotal testicular blood flow, volume and morphology.

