### Statistics and data-analysis

Baseline characteristics will be compared between men wearing the scrotal patches and controls by using Chi-squared tests for categorical variables and independent *t*-test for the normally distributed continuous variables. If the assumptions for normality are violated then non-parametric techniques will be applied. All statistical analyses will be conducted using SPSS or other validated statistical software and statistical significance reached when *P* <0.05 (two-tailed). Furthermore, parameter estimates will also be accompanied with 95% confidence intervals. No formal power calculation was done for this pilot study but we aim to invite sufficient eligible men to participate such that we actually recruit 20 men into each arm of the study (40 in total). This number was thought to be reasonable for estimating standard deviations of continuous variables and estimating recruitment to inform a definitive trial if required. Dichotomous data will be analysed as rates and continuous data as medians and ranges.

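### The primary outcome is a change from the qualifying semen sample with no stated scale or baseline adjustment; a log-scale ANCOVA would generally be more precise at almost no cost

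*Protocol article*

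**What the plan says.** - **Outcome** (protocol article, Outcome measures): "The primary outcome measure will be the change in sperm concentration after 90 days", in men wearing the patch against men not wearing it. Neither the scale of the change (million/mL, ratio or log) nor any covariate is given.
- **Baseline value** (Pre-randomisation data): "The results of the baseline semen analysis justifying inclusion into the study will be recorded in the research proforma". No separate baseline sample is described. Entry depends on that measurement (Participants): "sperm motility of < 32% and count of <15 million per millilitre".
- **Design** (Study design): "The study was designed as a randomised controlled trial and no stratification will be used", although eligible men run from mild to severe.
- **Tests** (Statistics and data-analysis): "Baseline characteristics will be compared between men wearing the scrotal patches and controls by using Chi-squared tests for categorical variables", and the independent t-test for normally distributed continuous variables. Then: "If the assumptions for normality are violated then non-parametric techniques will be applied". Continuous data are to be given as medians and ranges. Significance is two-tailed at 0.05, and estimates are to carry 95% confidence intervals.
- **Weight on the P value**: the Discussion paragraph of the Abstract would treat a significant improvement as definitive. The main Discussion would use a significant between-group difference to argue that 20 per arm had been enough.

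**The concern.** A simple change score subtracts the whole baseline value, which amounts to fixing the regression slope of follow-up on baseline at 1. Here the baseline is a noisy measurement on which men were selected for being low, so the true slope is expected to be below 1 and subtraction over-corrects. Noise is added to the comparison, and any chance difference in baseline between arms passes partly into the estimate, with the sign reversed.

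The article's statistics section directs its named tests at baseline characteristics. After proper randomisation, such a test only asks whether chance produced a difference already known to be due to chance. It neither measures nor removes the effect of that difference on the result.

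Precision and protection against chance imbalance are at stake in a 40-man trial whose authors intend to give weight to a significant primary result. The pilot aim is also affected: the sample size is justified partly by estimating standard deviations for a later trial, and the scale and adjustment decide which standard deviation that is.

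**Working it through.** **Inputs.** From the article: 20 men per arm, two-sided 0.05, baseline count below 15 million/mL, no stratification. The article gives no power, effect size, standard deviation or baseline/follow-up correlation (ρ), so there is no figure of its own to reproduce. Every variance, correlation and effect below is an assumption.

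**1. Chance imbalance.** The SD of the between-arm difference in mean baseline is √(2/20) = 0.316 baseline SDs. The probability that it exceeds 0.5 SD in either direction is P(|Z| > 0.5/0.316) = P(|Z| > 1.58) ≈ 0.11. Since 1.58 is below 1.96, a baseline significance test would not flag an imbalance of that size. With a true slope β, the change score shifts the estimate by (β − 1) × imbalance. For β of 0.64 to 0.80 (the range in simulation A below) and an imbalance of 0.5 SD, the shift is 0.36 × 0.5 = 0.18 down to 0.20 × 0.5 = 0.10 baseline SDs, in favour of the arm that started lower.

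**2. Closed form, equal variances at both visits.** Var(change) = 2·SD²·(1 − ρ) and Var(ANCOVA) = SD²·(1 − ρ²), so the ratio ANCOVA/change is (1 + ρ)/2. Estimating one slope with N = 40 multiplies this by about 1 + 1/(40 − 4) = 1.028. The detectable difference at 80% power is (1.96 + 0.84) × SD × √(2/20).

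| ρ | Variance ratio, with cost | Detectable difference, change → ANCOVA (SD units, before cost) | Power for 0.8 SD, change → ANCOVA (with cost) |
|---|---|---|---|
| 0.3 | 0.67 | 1.05 → 0.85 | 57% → 74% |
| 0.5 | 0.77 | 0.89 → 0.77 | 72% → 82% |
| 0.7 | 0.87 | 0.69 → 0.63 | 90% → 94% |
| 0.9 | 0.98 | 0.40 → 0.39 | about 100% for both |

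This overstates the gain here, because it ignores the cut at 15 million/mL.

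**3. Simulation A, baseline truncated at 15.** Assumptions: true median 8 or 20 million/mL, between-man log SD 0.8 to 1.0, within-man log SD 0.4 to 0.7, a 1.6-fold effect, five scenarios of 3,000 trials. The middle method is a t-test on change, replaced by a rank test if a normality check fails.

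| Scenario | t-test, raw change | t-test or rank rule | Log ANCOVA | Gain over t-test | Gain over rule |
|---|---|---|---|---|---|
| 1 | 65% | 72% | 76% | 11 | 4 |
| 2 | 35% | 41% | 46% | 11 | 5 |
| 3 | 42% | 51% | 57% | 15 | 6 |
| 4 | 48% | 55% | 59% | 11 | 4 |
| 5 | 23% | 32% | 35% | 12 | 3 |

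Log change had 5% to 12% more variance than log ANCOVA, so most of the gain over the raw t-test comes from the log scale.

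**4. Simulation B, different assumptions.** Population median 15 million/mL, only baselines below 15 kept, a 2-fold effect, 1,500 trials per setting. The log-ANCOVA/log-change variance ratio was about 0.86, 0.92, 0.97 and 1.01 at ρ = 0.3, 0.5, 0.7 and 0.9. At log SD 1.2, power for raw-change t-test / rank test on change / log ANCOVA was 28/42/44%, 33/47/52% and 49/62/68% at ρ = 0.3, 0.5 and 0.7. ANCOVA on the untransformed scale gave 27%, 31% and 50%, no better than the raw-change t-test, so naming the scale matters as much as naming the covariate. With no effect, rejection rates ran from 3% to 6% across all methods.

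**The case against.** The strongest reply is that the article defines an outcome and does not describe its analysis. ANCOVA with change as the response and baseline as covariate gives the same treatment effect as ANCOVA on the 90-day value (both on one scale), so a change outcome does not exclude adjustment. A reader might infer that the primary analysis is unadjusted and in absolute million/mL; the text says neither. The full protocol and analysis plan are not shown, and a model missing from a condensed article is not an error in itself. This stands, and it limits the point to a recommended improvement on what the article does fix: a change from the qualifying sample, named tests attached to baseline, and outcomes given as medians and ranges.

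Nor can the t-test-or-rank rule be called the trial's stated primary analysis. The sentence on normality follows the baseline tests, and extending it to outcomes is a reading. It serves here as a plausible comparator, and a fairer one than the raw t-test.

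A reader might also infer that selecting men on a low sample biases the result by regression to the mean. That drift occurs in both arms, and the article plans a comparison between arms, so the randomised contrast remains valid. No within-arm reading is proposed.

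Finally, this is a pilot without a power calculation, and a few points of assumed power would matter little if only feasibility were at stake. That carries some weight, but the article itself would rely on a significant primary result.

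**Conclusion.** The point holds as a matter of precision and chance imbalance, not validity. Log-scale ANCOVA gains about 3 to 6 power points over a t-test-or-rank rule and 11 to 15 over a raw-change t-test under simulation A. Simulation B ranks the methods the same way at ρ from 0.3 to 0.7, with a lead over ranks at log SD 1.2 of 2 to 6 points from the rounded figures. With the baseline truncated, the advantage over log change shrinks as ρ rises and is gone near 0.9. All these sizes rest on assumed variances, correlations and effects, and the simulations as described include no zero counts.

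Two further readings should be resisted. Serious imbalance is not likely: the chance of more than 0.5 SD is about 11%. Nor does the log-ratio model carry over automatically to motility and morphology, which can be bounded percentages.

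**What to change.** - Make the primary analysis an ANCOVA of log 90-day sperm concentration on allocated arm and log baseline concentration. Report the ratio of geometric means with its 95% confidence interval, which also supplies the interval estimate that medians and ranges do not.
- Prespecify how zero counts are handled. Men with severe disease are eligible, and an offset chosen after seeing the data could drive a log-scale result. Add a rank-based sensitivity analysis.
- Adjust each other semen outcome for its own baseline, on a scale suited to that outcome.
- Tabulate baseline characteristics by arm without P values.

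The cost is wording, one degree of freedom (1/36, about 3% of variance) and no new data, since both semen analyses are already collected. Recruitment began in October 2011 and the article reports four participants in November 2011, at most about 60 days later. No man had then reached day 90, so at that date the change could be made before any outcome was seen.

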### Statistics and data-analysis

Baseline characteristics will be compared between men wearing the scrotal patches and controls by using Chi-squared tests for categorical variables and independent *t*-test for the normally distributed continuous variables. If the assumptions for normality are violated then non-parametric techniques will be applied. All statistical analyses will be conducted using SPSS or other validated statistical software and statistical significance reached when *P* <0.05 (two-tailed). Furthermore, parameter estimates will also be accompanied with 95% confidence intervals. No formal power calculation was done for this pilot study but we aim to invite sufficient eligible men to participate such that we actually recruit 20 men into each arm of the study (40 in total). This number was thought to be reasonable for estimating standard deviations of continuous variables and estimating recruitment to inform a definitive trial if required. Dichotomous data will be analysed as rates and continuous data as medians and ranges.

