## Discussion

This study addresses an important but insufficiently explored area of male fertility. The potential economic benefits lie in the fact that the use of the scrotal cooling patches could, alongside the implementation of other important lifestyle changes in men with suboptimal sperm parameters, reduce the number of men who need expensive assisted conception. The study started recruiting in October 2011 and to date (November 2011) four men have been consented and are participating in the study. We have not encountered any operational challenges so far.

The study was also set up as a feasibility study and aims to evaluate factors which would be important should a definitive study be required. These include the recruitments rates and data for a power calculation. However, as we do not quite know how marked the effect of the scrotal patches will be, we decided to make the change in sperm count after 90 days of wearing the scrotal cooling patches compared with the control group the primary outcome measure, because if statistically significant differences between groups are identified, a *post hoc* sample size calculation could show that the current sample size (20 in each arm) was of sufficient power.

There was some discussion about the need or not for placebo patches in the control group. We decided against this as the placebo patches could raise the scrotal temperatures in men wearing them, resulting in a lowering of the sperm parameters in the control group introducing bias.

We have also chosen to assess testicular blood flow in this project as some studies show that this is associated with male fertility [14]. Endocrine factors and seminal fluid metabolomic biomarkers [15] have also previously been evaluated and shown to be related to male fertility. We have therefore also used the opportunity to investigate whether changes in endocrine levels and serum metabolomic profiles, which are possible surrogate markers of male fertility, occur as a result using the scrotal cooling patches.

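### The sample size rests on estimating standard deviations, but the stated analysis of continuous data (medians and ranges) leaves the SD out and does not say which between-group estimate carries the promised 95% CI

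*Protocol article*

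**What the plan says.** All the main statements are in the article's Statistics and data-analysis section.

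- On sample size: "No formal power calculation was done for this pilot study". The target is 20 men per arm, 40 in total, and the reason given is: "This number was thought to be reasonable for estimating standard deviations of continuous variables and estimating recruitment to inform a definitive trial if required".
- On continuous data, in the sentence directly after: "Dichotomous data will be analysed as rates and continuous data as medians and ranges".
- On precision, earlier in the same paragraph: "parameter estimates will also be accompanied with 95% confidence intervals".

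The t-test, with a non-parametric fallback, is named for comparing baseline characteristics. No sentence plans a mean or an SD for any outcome. The primary outcome (Outcome measures section) is continuous: the 90-day change in sperm concentration, patch against no patch. The Discussion restates the feasibility aim when it lists what a definitive study would need: "These include the recruitments rates and data for a power calculation".

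**The concern.** Two neighbouring sentences pull in different directions. One says the trial is this size so that SDs can be estimated; the next sets a rule for continuous data that does not produce an SD. The rule makes no exception for the primary outcome, and its verb covers analysis, not only description. This is therefore not a detail left to a fuller document. It is a stated rule that does not match the stated purpose.

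What is at stake is the feasibility output. A reader planning the next trial from a report that followed this sentence would find a median and a range per arm. An SD could be recovered from these only by assuming a distribution. That reader would also not know whether the confidence interval belongs to a median in one arm, a difference in medians, a location shift or a difference in means.

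**Working it through.** **The plan's own figure.** The article assumes no power, effect size or SD, so 40 can be neither reproduced nor refuted. The check is whether the planned summary delivers what 40 was chosen for.

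**Inputs.** From the article: n = 20 per arm, 40 in total, two-sided 5% level. Assumed here: normal data and no dropout, unless stated otherwise. The log-normal case uses a log-scale SD of 0.8 purely as an illustration; the article gives no SD for sperm concentration.

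**1. How the range behaves.** The expected range of normal data, by simulation, is 3.53 SDs with 16 men, 3.73 with 20 and 4.32 with 40. The same population therefore shows a range 4.32 / 3.53 = 1.22 times as wide at 40 men as at 16.

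**2. Recovering an SD from the range at n = 20** (200,000 simulated samples; results relative to the true SD):

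| Data | Estimator | Central 95% | Coefficient of variation |
|---|---|---|---|
| Normal | SD itself | 0.68 to 1.32 | 16.4% |
| Normal | range / 3.735 | 0.66 to 1.42 | 19.5% |
| Log-normal (assumed 0.8) | SD itself | 0.42 to 1.94 | 45% |
| Log-normal (assumed 0.8) | range / 3.735 | 0.40 to 2.25 | 53% |

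The common shortcut range / 4 averages 0.934 of the true SD for normal data, about 7% low. The range-based value is noisier in both cases, but not by much. Under skew, most of the noise comes from the skewness and not from the use of the range. That is a reason to choose a suitable scale before quoting any SD.

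**3. Precision of the SD if it is reported.** The 95% limits, as multiples of the estimate, are √(df / χ²(0.975, df)) and √(df / χ²(0.025, df)).

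- One arm, df = 19: 0.760 to 1.461.
- Both arms pooled, df = 20 + 20 − 2 = 38: 0.817 to 1.289.

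For a continuous endpoint the required N is proportional to the variance. The pooled limits squared are 0.668 and 1.661, a ratio of 1.661 / 0.668 = 2.49. Adjusting for baseline costs one degree of freedom and hardly moves these limits; dropout widens them.

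**4. Are confidence intervals possible with medians?** Yes. With n = 20, the 6th and 15th ordered values bound the median with exact coverage 1 − 2·P(X ≤ 5), X ~ Binomial(20, 0.5), which is 95.9%. A location shift between arms has a Hodges-Lehmann interval. For comparison, a difference in means has a 95% half-width of t(0.975, 38) × √(2/20) = 0.64 SD. The promised intervals are therefore available on either route, and the text does not say which route is meant.

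**The case against.** The strongest reply is that nothing is lost. The investigators will hold each man's values, the article names SD estimation as a purpose, and a default summary does not forbid computing an SD. Nobody in the trial team would need to work back from a range. This is correct, and it limits the finding: the text is inconsistent, but the data are not compromised. It does not remove the finding, because the stated rule still omits the quantity used to justify the sample size.

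A reader might infer two stronger things that the documents do not support.

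- **That medians rule out the promised confidence intervals.** They do not. Exact intervals exist for medians and for location shifts, and the article promises 95% intervals in a separate sentence that the medians rule does not cancel. Only the choice of estimate is open.
- **That the trial would fail to supply the key input for its successor.** The SD remains computable. The Discussion also foresees a later trial with live birth as primary outcome, for which event rates matter and a semen SD is not the main input. The SD matters to the extent that the statistics section itself asks for it.

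It can also be said that an SD from 20 per arm is imprecise in any pilot, and that how a later trial allows for this is for that trial to decide. That stands. Sizing from an upper confidence limit is one convention among several, and its absence here is not an error.

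**Conclusion.** The point holds in a limited form. The paragraph justifies 20 per arm by SD estimation and then fixes a summary that leaves the SD out. It puts in its place a range that depends on n and on two men and is not an interval estimate. It promises 95% intervals without tying them to a between-group estimate.

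The consequence is modest: a mismatch between purpose and stated analysis, recoverable from the individual data, with no error in any number. The useful size to state is the precision of the SD: 0.82 to 1.29 times the estimate pooled (38 df), or 0.76 to 1.46 from one arm (19 df). The pooled limits correspond to 0.67 to 1.66 times the N implied by the point estimate for a continuous endpoint. These limits assume normality on the analysis scale and 40 completers. The 53% and 45% figures rest on the illustrative log SD of 0.8 and should not be read as facts about this population.

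**What to change.** Replace the last sentence of the Statistics and data-analysis section, as it concerns continuous data, with a rule along these lines:

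- For sperm concentration and the other semen outcomes, report the mean and SD of the 90-day change by arm. Use a log or other suitable scale if the data are skewed, and state in advance how zero counts are handled, since a plain log fails for them.
- Report the pooled SD, or the residual SD after baseline adjustment, with its 95% CI, so that its imprecision is visible to anyone planning a further trial.
- Report the between-group difference, adjusted for the baseline semen value already collected before randomisation, and name it as the estimate that carries the 95% CI.
- Keep medians for description only, with the interquartile range in place of the range.

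The treatment of dichotomous data can stay. N, design and data collection do not change. The cost is a little more analysis and an open statement that the SD from this trial is imprecise.
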